## 7.5 Criteria for Placing the Study on Hold

If a dose of vaccine is considered significantly reactogenic (see below), additional vaccinations will be suspended until a thorough review by the independent Medical Monitor and SMC and discussion between the Principal Investigators, the Medical Monitors, and Sponsors. Resumption of vaccinations will start only if all parties agree to a resumption of vaccination. The communications from the SMC will subsequently be forwarded by the investigators to the respective IRBs.

The following criteria will be used to define significant reactogenicity:

1. One or more volunteers experience an SAE (as defined in **Section 7.1.2** in this protocol) that is determined to be possibly, probably, or definitely related to the vaccine (as defined in **Section 7.2.3** in this protocol), **OR**
2. One or more volunteers experience anaphylaxis that is probably or definitely related to the vaccine, **OR**
3. Occurrence of any severe clinical illness in one or more volunteers that is not explained by another diagnosis unrelated to vaccination, **OR**
4. Two or more volunteers experience a Grade 2 or higher laboratory abnormality, with the exception of CPK. In the case of CPK, if in the absence of other explanation (vigorous unaccustomed exercise) one volunteer experiences a Grade 3 or higher elevation of CPK or if two or more volunteers experience a Grade 2 elevation of CPK.
5. One volunteer experiences a Grade 3 clinical AE that is determined to be probably or definitely related to the vaccine, with the exception of isolated Grade 3 local erythema or swelling.
6. The principal investigator (PI) may, using discretion, ask for the study to be placed on hold and an SMC meeting to be held for any single event or combination of multiple events which, in professional opinion, jeopardize the safety of the participants or the reliability of the data.

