### 7.1.2 Serious Adverse Event (SAE)

An SAE is an AE, whether considered related to the investigational vaccine or not, meeting one of the following conditions:

1. Death during the period of protocol-defined surveillance.
2. Life threatening: defined as an event that places a subject at immediate risk of death at the time of the event and does not refer to an event that hypothetically might have caused death were it more severe.
3. Hospitalisation during the period of protocol-defined surveillance: defined as at least an overnight stay in the hospital or emergency ward for treatment that would have been inappropriate if administered in the outpatient setting.
4. Results in a congenital anomaly or birth defect.
5. Results in a persistent or significant disability or incapacity: defined as a substantial disruption of the study participant’s ability to carry out normal life functions.
6. Any other important medical event that may not result in death, be life threatening, or require hospitalization, may be considered a serious AE when, based upon appropriate medical judgment, the event may jeopardize the subject and may require medical or surgical intervention to prevent one of the outcomes listed above.

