## 7.4 Adverse Event Monitoring

### 7.4.1 Local Medical Monitor

An independent local Medical Monitor has been appointed for oversight of safety in this trial. The local Medical monitor will be available to advise the investigators on trial-related medical questions or problems, and act as a representative for the volunteers’ welfare. Additionally, the local Medical Monitor may ask to convene a safety monitoring committee (SMC) meeting for review of any safety issue or adverse event. The Medical Monitor will review all SAEs.

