### 7.4.2 Safety Monitoring Committee

The sponsor (QIMR) in consultation with MVI will select three independent monitors to form the Safety Monitoring Committee to advise the site and the study investigators on the trial safety. The SMC will be independent of sponsors and the clinical trial site. The SMC’s primary responsibility will be to monitor volunteer safety. The SMC will meet at the nominated schedule (Table 1) following the immunizations of the 10 µg and 40 µg dose groups to approve further vaccination in selected cohorts and dose escalation, and whenever the need should arise. The SMC will review cumulative safety data for evidence of study-related AEs, adherence to the protocol, and factors that may affect outcome or study data such as protocol violations and losses to follow-up. At each meeting the SMC will make a recommendation regarding the safe continuation of the study. If no stopping criteria are met (**Section 7.5**), with the approval from the SMC the trial will proceed.

The Principal Investigators are responsible for ensuring that the SMC is aware of all new safety information.

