### 7.5.1 Criteria for Stopping an Individual Volunteer’s Further Vaccination

A. *Local Reactions*: Investigator discretion

B. *Systemic AEs*: Individual participants will be withdrawn from further immunisation if they develop a Grade 3 AE beginning within two days after immunisation and persisting at Grade 3 48 hours if the AE is malaise, myalgia, fatigue, fever, headache, or joint pain, or if the subject has any other Grade 3 AE considered to be associated with vaccination, or if they have any vaccine-related SAE.

C. *Laboratory AEs*: Individual participants will be withdrawn from further immunisation for any Grade 2 laboratory AE that lasts for ≥48 hours or any Grade 3 laboratory AE considered possibly, probably or definitely associated with immunisation.

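### Section 7.5 item 4 has no one-volunteer trigger for non-CPK laboratory values, so a single vaccine-related, non-serious Grade 3 result forces no hold, unlike Grade 3 CPK or a related Grade 3 clinical AE

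*Protocol*

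**What the plan says.** Protocol Section 7.5 lists what suspends vaccination until review by the Medical Monitor and the SMC.

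- Items 1 to 3 need, in one volunteer, a related SAE, related anaphylaxis, or a severe clinical illness not otherwise explained.
- Item 4, laboratory values other than CPK: "Two or more volunteers experience a Grade 2 or higher laboratory abnormality, with the exception of CPK".
- Item 4, CPK without another explanation: "one volunteer experiences a Grade 3 or higher elevation of CPK", or two volunteers at Grade 2.
- Item 5: "One volunteer experiences a Grade 3 clinical AE that is determined to be probably or definitely related to the vaccine", except isolated Grade 3 local erythema or swelling.
- Item 6: the principal investigator "may, using discretion, ask for the study to be placed on hold".

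For the individual volunteer, Section 7.5.1 C ends vaccination after "any Grade 3 laboratory AE considered possibly, probably or definitely associated with immunisation", and also after a Grade 2 laboratory AE lasting 48 hours or more.

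Other provisions bear on a single abnormal result:

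- Section 7.1.2, condition 6: an important medical event "may be considered a serious AE when, based upon appropriate medical judgment, the event may jeopardize the subject".
- Section 7.4.1: the Medical Monitor "may ask to convene a safety monitoring committee (SMC) meeting for review of any safety issue or adverse event".
- Section 7.4.2: the SMC meets on the Table 1 schedule "to approve further vaccination in selected cohorts and dose escalation, and whenever the need should arise", and the principal investigators must keep it aware of new safety information.
- Section 7.5.2: the sponsors can convene the SMC over further safety concerns.

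Section 3.1 staggers the 40 µg cohort (five volunteers, then ten at least four weeks later) and relies on the Section 7.5 rules to suspend the trial pending SMC review.

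**The concern.** At study level the protocol treats one severe event as enough for a mandatory pause when it is an unexplained CPK rise or a probably or definitely related clinical AE. A Grade 3 headache judged probably related stops dosing for everyone. A Grade 3 ALT, neutrophil, platelet or creatinine result with the same attribution does not, unless a second volunteer also has a Grade 2 or higher value. Past interest in muscle damage with this adjuvant can explain a strict CPK rule. It does not explain why other laboratory toxicity ranks below clinical toxicity of the same grade and attribution.

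What is at stake is the stagger in the higher-dose cohort of a formulation not yet given to humans. The lead five have haematology and biochemistry on Days 3 and 14, so a Grade 3 result would normally be known before the other ten are dosed. On Table 1's minimum timings the lead five are dosed at Week 4 and the ten at Week 8, and the first scheduled SMC meeting is at Week 11. First doses may be later than these minimums. Nevertheless, no scheduled meeting is placed between the two subgroups, so for this event the pause rests on judgement.

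**Working it through.** **Step 1: test the event against each criterion.** Take one volunteer with a non-serious, vaccine-related Grade 3 value from Appendix 3: ALT/AST above 5 x ULN, ANC below 0.50, platelets 20-99, or creatinine above 3 x ULN.

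| Item | Requires | Met? |
| --- | --- | --- |
| 1 | a related SAE | No, the value is non-serious |
| 2 | anaphylaxis | No |
| 3 | severe clinical illness | No, it is a laboratory value |
| 4, non-CPK | two volunteers at Grade 2 or higher | No, only one |
| 4, CPK | CPK | No |
| 5 | a clinical AE | No |
| 6 | the PI's request | By discretion only |

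The same holds for a non-serious Grade 4 value such as platelets below 20.

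**Step 2: inputs for size.** The protocol gives no operating characteristic for the hold rule and no laboratory rates. Its only event rate is 15% for any serious or severe AE (Section 9.1.4). With 12 active volunteers, 1 - 0.85^12 = 0.858 against the stated 0.80. That difference is a separate matter and nothing below depends on it.

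All rates below are assumptions:
- p = related Grade 3 or higher non-CPK value, per active volunteer: 1%, 5% or 15%.
- b = any other non-CPK Grade 2 or higher value, per volunteer: 0%, 3% or 10%.

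Dosed before the ten: 12 active in Cohort 1 and about 4 active among the lead five, so 16 active out of 20. The other 19 are 15 + 5 - 1.

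**Step 3: lead five only.** Exactly one of 4 active: 4p(1-p)^3 = 0.039, 0.171, 0.368. No such value in Cohort 1's 12 active, multiply by (1-p)^12: 0.034, 0.093, 0.052. No other Grade 2 or higher value among the 19 at b = 3%, multiply by 0.97^19 = 0.561: 0.019, 0.052, 0.029.

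**Step 4: either cohort.** Exactly one of 16 active has the value and item 4 stays unmet: 16p(1-p)^15 x (1-b)^19.

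| p | b = 0 | b = 3% | b = 10% |
| --- | --- | --- | --- |
| 1% | 14% | 8% | 2% |
| 5% | 37% | 21% | 5% |
| 15% | 21% | 12% | 3% |

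**Step 5: let Grade 2 values accompany Grade 3 values.** A vaccine that causes Grade 3 changes would plausibly cause Grade 2 changes too. With p3 and p2 the Grade 3 and Grade 2-only rates in the 16 active, the chance is 16 x p3 x (1 - p3 - p2)^15:

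- p3 = 5%, p2 = 5%: 0.80 x 0.90^15 = 16%
- p3 = 5%, p2 = 10%: 0.80 x 0.85^15 = 7%
- p3 = 15%, p2 = 15%: 2.40 x 0.70^15 = 1%

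**Step 6: extra holds from the fix if the vaccine has no effect.** With g the background rate of a new Grade 3 value and f the share that passes the relatedness test, the chance over 30 volunteers is 1 - (1 - g x f)^30. At g = 0.1%, 0.5% and 1% with f = 25% this is 0.7%, 3.7% and 7.2%. At g = 0.5% and f = 50% it is 7%. At g = 1% and f = 100% it is 26%. The low f values suit a probable-or-definite test better than a test that also admits possible relatedness.

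**The case against.** Four arguments weigh against the point.

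**Individual and study rules are meant to differ.** One might infer that Section 7.5.1 C contradicts item 4, because it stops the volunteer for the very event that does not hold the study. The documents do not support that. The individual rules are set lower than the study rules in other places too: 7.5.1 B needs only association with vaccination where item 5 needs probable or definite relatedness, and 7.5.1 C acts on one persistent Grade 2 laboratory value where item 4 needs two volunteers. This is consistent tiering. The comparison that counts is with the other study-level triggers, and there the mismatch remains.

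**The event would not go unseen.** One might infer that a related Grade 3 value could pass without review. In fact the principal investigators must keep the SMC informed (7.4.2). The Medical Monitor, the principal investigator and the sponsors can each prompt a meeting or a hold, and classification as an SAE would trigger item 1. This stands as mitigation. Informing the SMC does not suspend dosing, however, and every route to a hold is a matter of judgement.

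**The rule fits the known risks, and item 4 is already sensitive.** Section 3.1 justifies the stagger by delayed local reactions, and the clinical background describes no hepatic, renal or haematological signal. Item 4 counts any two volunteers at Grade 2 or higher, without regard to relatedness, test, arm or timing. This lowers the size of the problem but does not explain the difference from item 5.

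**The larger probabilities are soft.** The 37% and 21% in the b = 0 column assume no other Grade 2 or higher value in anyone, and a 15% rate of related Grade 3 laboratory values has no support in the protocol. This objection is right, and those figures should not be used as estimates.

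**Conclusion.** The point holds as a gap in a mandatory hold rule. One non-serious, vaccine-related Grade 3 or higher non-CPK laboratory value forces no hold, which is out of line with the one-volunteer triggers for CPK and for related clinical AEs. It is not a contradiction within the protocol, nor evidence that such an event would be ignored.

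Its size depends wholly on assumed rates. Where other Grade 2 or higher values are allowed for, the chance that the gap matters before the remaining ten are dosed is 1% to 8% in most of the scenarios worked. It is 12% to 21% where such values are assumed scarce relative to Grade 3 values. Single-digit percent is the reasonable expectation. The case rests on the wording of the rule rather than on any one rate. Cheap improvement, minor to moderate priority.

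**What to change.** Add to the first sentence of item 4: *or one volunteer has a Grade 3 or higher laboratory abnormality other than CPK, new or worse than in the pre-dose sample, judged probably or definitely related to the vaccine.* This uses item 5's relatedness standard. Admitting possible relatedness would make the laboratory trigger looser than the clinical one and cause more holds. Leave the two-volunteer Grade 2 trigger and the CPK sentence as they are.

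The change needs no extra volunteers, samples or unblinding. Its cost is an occasional additional pause for Medical Monitor and SMC review, about 1% to 7% over the whole trial at the f = 25% assumption above if the vaccine has no effect. A pause lifts only when all parties agree, doses 2 and 3 have windows of ±7 days, and volunteers are not replaced after the first vaccination in a cohort. A long pause could therefore delay or lose doses, so review should be prompt.

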### 7.5.1 Criteria for Stopping an Individual Volunteer’s Further Vaccination

A. *Local Reactions*: Investigator discretion

B. *Systemic AEs*: Individual participants will be withdrawn from further immunisation if they develop a Grade 3 AE beginning within two days after immunisation and persisting at Grade 3 48 hours if the AE is malaise, myalgia, fatigue, fever, headache, or joint pain, or if the subject has any other Grade 3 AE considered to be associated with vaccination, or if they have any vaccine-related SAE.

C. *Laboratory AEs*: Individual participants will be withdrawn from further immunisation for any Grade 2 laboratory AE that lasts for ≥48 hours or any Grade 3 laboratory AE considered possibly, probably or definitely associated with immunisation.

### 7.5.2 Process for Study Discontinuation

If the Principal Investigators, Sub-Investigators, Medical Monitor or sponsors have any further safety concerns, the SMC can be convened by the sponsors to review the safety data. The committee will provide verbal and hard copy written reports to the investigators and sponsors, who will then forward to the appropriate HREC/IRBs. Findings of a serious and immediate nature including any recommendations to modify or discontinue all or part of the study must be reported immediately in verbal and written form. Under circumstances where there are safety concerns that warrant no immunisation of a cohort, no further immunisations will be performed, and the Sponsors and all IRB/HRECs and Regulatory authorities will be promptly notified. All immunized participants will be followed for safety until resolution of their AEs or until at least 30 days after the last immunisation.

# 8.0 Data Collection and Monitoring

## 8.1 Source Documentation

Complete source documentation (laboratory test reports, hospital or medical records, etc.) is required for every study subject for the entire duration of the study. Clinical Report Forms (CRFs) and volunteer symptom diaries will be used to record data for participants enrolled in the study. The Investigator is responsible for the accuracy and completeness of the data reported to the Sponsor in the CRFs and diaries. Data reported in the CRFs derived from source documents should be consistent with source documents or the discrepancies should be explained.

## 8.2 Study Documentation

Study-related documentation will be completed as required by the HREC/IRBs, the Sponsor, ICH Guidelines, and regulatory authorities and maintained at the trial site. Continuing review documentation will be submitted by the Investigators to the HREC/IRBs as specified by each committee. An annual report will be submitted by the investigator to the HREC/IRB on the anniversary approval date for MSP2/ISA720 malaria vaccine went into effect. These reports will provide a brief description of the progress of the investigation as outlined in NHMRC National Statement and will include any revisions of the protocol.

The Investigator will maintain adequate records of the disposition of the investigational product, including dates, quantity and use by participants. If the study is terminated, suspended or completed, final disposition of unused vaccine supplies will be determined by Q-Pharm, in conjunction with the Sponsors.

In addition to the study-related documentation required by the regulatory authorities, the Sponsor (QIMR) will also submit a final study report to the Funding Sponsor (MVI). The final study report will be completed after the safety and immunogenicity data from all study visits have been compiled and analysed. A Clinical Safety Report will be prepared by the CRO and submitted to the Sponsors after database lock and statistical analysis is completed. The Sponsor (QIMR) will prepare the final Clinical Study Report.

## 8.3 Access to Study Documentation:

The principal investigator will permit trial-related monitoring, audits, IRB/ethics review, regulatory inspections (national or international) by providing direct access to source/data documents when requested.

## 8.4 Clinical Database

In addition to the primary CRF maintained on paper, an electronic clinical database will be built to facilitate management of clinical data, and to automate data quality processes. The database will be built and managed in accordance with FDA 21CFR11. Data from the paper CRFs will be double entered into the database, and reconciled. Automated edit checks for data quality will be programmed. Data items failing such quality checks will be queried to the site. 10 % of data base records will be audited for quality assurance purposes.

Full details of the data management process, including the data dictionary, edit checks and query handling will be documented in a data management plan.

## 8.5 Retention of Records

Trial-related documents will be maintained by the site for a period of 2 years after final marketing approval of the vaccine, or for 2 years following the formal discontinuation of clinical development of the product or per local law regulations, whichever is longer. The Sponsor is required to inform the Investigator as to when such documents need no longer be retained. Storage of all trial-related documents will be such that confidentiality will be strictly maintained.

## 8.6 Protocol Revisions

No revisions to this protocol will be permitted without documented approval from both the Sponsors and the IRBs that granted the original approval for the study. Furthermore, in the event of a medical emergency, the Investigator shall perform any medical procedures that are deemed medically appropriate. The Investigator must notify the Sponsor of all such occurrences. Any change to the protocol will be submitted to the participating IRBs as a protocol amendment and changes not affecting risk to volunteers may be expedited, as appropriate.

## 8.7 Clinical Investigator’s Brochure

Investigators will receive the current version of the Clinical Investigator’s Brochure, which comprehensively describes all the available preclinical and clinical experience with the experimental vaccine and adjuvant. If relevant new information becomes available during the course of the trial, the Investigators will receive a revised Investigator’s Brochure or an amendment to the current version.

## 8.8 Study Monitoring

The Sponsor (QIMR) will monitor through delegated responsibility via a CRO (Clinical Network Services), all aspects of the study, with respect to current Good Clinical Practices (GCP), and ICH Guidelines for compliance with applicable government regulations. Prior to the start of the study, the Investigator will be informed of the frequency of monitoring visits and will be given reasonable notification prior to each visit. The objectives of a monitoring visit will be to verify the prompt reporting of SAEs, to check the availability of the signed Informed Consent, GCP adherence to the protocol, and to compare CRFs with source data for completeness and accuracy. During the monitoring visit, the Investigator (and/or designee) and other study personnel should be available to discuss the study. Study documents must be available for review throughout the course of the study.

# 9.0 Statistical Considerations

## 9.1 General Design

The goal of this Phase 1 vaccine trial is to demonstrate safety and immunogenicity of MSP2-C1/ISA720 malaria vaccine in healthy adult human volunteers.

### 9.1.1 Description of the Statistical Methods to Be Employed

The purpose of this trial is to estimate event rates and patterns of adverse events for safety as well as immune responses for the three different doses of the study vaccine. This section briefly describes the statistical methods to be used. A detailed Statistical Analysis plan will fully describe the methods and will be finalized prior to lock of the study database. The analytic plan will discuss the planned approaches to missing data.

Any deviations from the statistical analysis plan will be documented and justified in the statistical report.

Estimates will be presented with their 95% confidence intervals. Analysis will involve both descriptive exploratory methods, and hypothesis driven significance testing. In particular, the immunologic response and the adverse events for each of the 30 volunteers (Active versus ISA720 Control) will be presented as individual graphs.

### 9.1.2 Analyses for Primary Objective (safety)

To assess the safety and tolerability of three immunisations at two dosage levels of the MSP2-C1/ISA720 vaccine in healthy malaria-naive volunteers

The incidence of AE and SAEs will be tabulated by treatment group (with the pooled ISA720 Control patients representing one group), System Organ Class and Preferred Term. Incidence in each treatment group will be compared with that in the pooled ISA720 Control group using Fisher's exact test (correcting for multiple comparisons across AEs using Holm's method (37). Separate assessments of systemic and local reactions will be performed. The overall number and percentage of volunteers with at least one AE (and SAE) will be tabulated after each vaccination and over the entire study period. In addition, longitudinal comparisons will be made for each treatment group using Lidell’s exact version of McNemar’s test. The incidence, intensity, and relatedness to vaccination of individual symptoms will be calculated for each dose and study arm. The incidence, intensity and relatedness to vaccination will be calculated for each treatment group.

If any clinically significant deviations from normal occur in routine laboratory test results and/or vital signs, they will be analyzed using a longitudinal linear mixed model, with Treatment Group and Time as fixed effects, and subject and times within subject as random effects. An appropriate covariance structure will be selected for the longitudinal error term. These analyses will be repeated for change from baseline values, where the baseline is given by pre-dose values.

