## 3.2 Sample Size and Estimated Duration of Study

A total of 30 volunteers will be vaccinated in 2 cohorts of 15 (see **Section 9.1.4** for a justification of the sample size). Twelve in each cohort will be randomized to receive 10 or 40 µg of MSP2-C1 formulated in ISA720; 3 in each cohort will be randomized to receive ISA720 Control. The trial is expected to last for a total of 56 weeks. Each volunteer will be followed for 48 weeks from the time of the first injection.

It is estimated that up to 150 volunteers will need to be screened to complete enrolment.

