### 9.1.3 Analyses for Secondary Objectives (Immunogenicity)

### 9.1.3.1 Characterise the humoral and cellular immune responses to the MSP2-C1/ISA720 vaccine:

Anti-MSP2 antibodies (anti-MSP2 3D7 & anti-MSP2 FC27- Total and Ig G subtype) will be measured by ELISA for each serum sample. Immunogenicity responses will be described by vaccine and dose group, over time. Individual responses will be described over time and stratified by dose cohort. Antibody titres will be measure on Days 0, 28, 84, 112, 168, 196, and 336). The primary immunogenicity endpoint will be evaluation of sera taken at 28 days after each vaccination, and at six months after the final vaccination as listed in the schedule of visits (Appendix 1).

Antibody responses will be analysed using a longitudinal linear mixed model, with MSP2 serotype, Dose and Time as fixed effects, and Subject and Times within Subject as random effects. An appropriate covariance structure will be selected for the longitudinal error term. Because of the small sample size of this study, statistical tests will be performed without correction for multiplicity. A nominal Type I error rate of 10 percent will be used. Parameter estimates will be obtained using the REML algorithm (38). Contrasts will be generated to evaluate MSP2 serotype and Dose effects at each time point. Formal statistical tests will assess whether the response is monotone (low dose < medium dose < high dose) for the 2 doses of vaccine being tested to look for a dose response.

The vaccine dose level which induces the highest concentrations of MSP2 specific IgG will be determined graphically.

Additionally, the cell mediated responses (T cell proliferation, cytokines) will be performed on Days 0, 28, 112, 196, and 336. T cell proliferation and cytokines will be analysed in the same way, using a longitudinal linear mixed model. Analyses will include (but not be limited to) contrasts to examine difference between MSP2 serotypes and Dose levels at each time point. All of these analyses will be repeated using pre vaccination (day 0) values as a covariate.

The following parameters will be summarised by simple descriptive statistics:

Parameter 1: The ability of the vaccine induced antibody to inhibit parasite growth as measured by the in vitro growth inhibition assay (GIA)

Parameter 2: The relationship between anti-MSP2 antibody levels and degree of in vitro parasite growth inhibition.

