### 9.1.4 Sample Size

This study is powered to provide sufficient safety data on an adult population living in an area without malaria. A group size of 12 volunteers per dose will receive the MSP2-C1/ISA720 malaria vaccine and a total of 9 participants, 3 per dose cohort will receive ISA 720 Control vaccine as a control. This will give a probability of 0.80 for detecting one or more serious or severe AEs that occurred with a probability of 0.15 per volunteer.

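### Section 9.1.2 applies Holm's correction to very small adverse-event comparisons and models laboratory and vital-sign data only after a clinically significant deviation has been seen

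*Protocol*

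**What the plan says.** **Adverse events.** Protocol Section 9.1.2 (primary objective, safety) tabulates adverse events by System Organ Class and Preferred Term. It compares each treatment group with control by Fisher's exact test, "with the pooled ISA720 Control patients representing one group" and "correcting for multiple comparisons across AEs using" Holm's method. It gives neither the number of terms nor the significance level for these tests.

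**Group sizes.** Section 9.1.4: "A group size of 12 volunteers per dose will receive the MSP2-C1/ISA720 malaria vaccine". Section 3.2: "3 in each cohort will be randomized to receive ISA720 Control". With two cohorts, the pooled control group is 6.

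**Immunogenicity.** Section 9.1.3.1 takes the opposite line: "Because of the small sample size of this study, statistical tests will be performed without correction for multiplicity". It sets a nominal 10% level.

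**Laboratory and vital signs.** Section 9.1.2: "If any clinically significant deviations from normal occur in routine laboratory test results and/or vital signs, they will be analyzed" by a longitudinal linear mixed model. The analysis is then repeated on change from the pre-dose value. What counts as clinically significant for this purpose is not defined there.

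**The concern.** Two stated rules sit badly with a first-in-human safety objective.

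1. In a safety screen the costlier error is usually the missed signal. Holm's correction guards against false positives, and its bar rises with the number of terms in the family, so unrelated minor events make a real difference harder to declare. The protocol accepts small sample size as a reason to drop correction for a secondary objective, then imposes correction on the primary objective in the same 30 volunteers.
2. A model that is run only when clinically significant deviations occur is selected on the outcome it is meant to describe. A shift in, say, ALT, creatinine or CPK that stays below the trigger would never be compared between groups by the planned model, although the samples are drawn on schedule.

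At stake is how the safety tables are read. A column of non-significant adjusted p-values, or the absence of a laboratory analysis, carries little information here.

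**Working it through.** **The plan's own figure.** The protocol gives no power for the between-group comparisons. Its only safety figure (Section 9.1.4) is a probability of 0.80 of seeing at least one serious or severe event at a rate of 0.15 per volunteer. For 12 volunteers this is 1 − 0.85^12 = 0.858; 0.80 fits 10 volunteers (1 − 0.85^10 = 0.803). That figure concerns a single group, so it says nothing about the Fisher comparisons. The mismatch is a separate matter.

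**Inputs.** 12 vaccinees per dose (Sections 3.2 and 9.1.4); 2 × 3 = 6 pooled controls (Sections 3.2 and 9.1.2). Assumed, because the protocol does not state them: two-sided 5% level, and m = 5 to 50 terms in the Holm family.

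**Fisher p-values with 0/6 controls.** For a events among vaccinees, the table has probability C(12,a)/C(18,a). The two-sided p adds every table with the same total that is no more probable.
- 6/12: (924 + 72 + 1)/18564 = 0.054
- 7/12: (792 + 396 + 12)/31824 = 0.038
- 8/12: (495 + 66)/43758 = 0.013
- 9/12: (220 + 220)/48620 = 0.0090
- 10/12: 66/43758 = 0.0015
- 11/12: 12/31824 = 0.0004

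**Holm's first step.** The smallest p must be at most 0.05/m. Power is the binomial probability summed over all tables that meet the threshold.

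| Terms (m) | Threshold | Needed vs 0/6 | Power, 80% vs 10% | Power, 50% vs 0% |
|---|---|---|---|---|
| 1 (unadjusted) | 0.05 | 7/12 | 83% | 39% |
| 5 | 0.01 | 9/12 | 53% | 7% |
| 10 | 0.005 | 10/12 | 40% | 2% |
| 20 | 0.0025 | 10/12 | 32% | 2% |
| 30 | 0.00167 | 10/12 | 32% | 2% |
| 50 | 0.001 | 11/12 | 17% | 0.3% |

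These are powers for one term at the strictest step. Thresholds relax if other terms are rejected first.

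**Sensitivity.**
- At a 10% level the unadjusted need is 6/12; Holm needs 8/12 for 5 terms, 9/12 for 10 and 10/12 for 20 to 50.
- Section 9.1.4 gives "a total of 9 participants, 3 per dose cohort will receive ISA 720 Control vaccine as a control", which conflicts with the two-cohort design. With 9 controls the need is 5/12 unadjusted, 8/12 for 10 terms, 9/12 for 20 to 30 and 10/12 for 50. The pattern is the same.

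**What Holm does not explain.** At the 11% delayed-reaction rate cited in Section 2.3.3, against 0% in controls, power is about zero with or without correction. The intervals are also wide: the exact 95% upper limit is 26.5% for 0/12 and 45.9% for 0/6.

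**Laboratory trigger.** No arithmetic is needed. Section 6.4 and Appendix 1 schedule haematology, creatinine and liver enzymes at 11 study days from Day 0 (0, 3, 14, 56, 84, 87, 98, 140, 168, 171, 182), and CPK at 6 of them (0, 14, 84, 98, 168, 182). Section 6.4 has vital signs recorded at every clinic visit. The data for an unconditional analysis are therefore already collected; only the rule for using them is conditional.

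**The case against.** The strongest reply is that Holm governs only the Fisher p-values. Section 9.1.1 states an estimation purpose, and promises 95% intervals and individual graphs for all 30 volunteers. Section 9.1.2 tabulates incidence, intensity and relatedness by group. Grading (Section 7.2.2), committee review (Section 7.4.2) and the hold rules (Section 7.5) work without any p-value, and laboratory changes enter them as adverse events whether or not the model is run. This stands. A reader might infer that the primary safety analysis as a whole is built to miss signals, or that a finding of no difference is almost guaranteed; the protocol does not support either. Nor does it say that non-significance would count as evidence of safety.

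Group size also stands as a main limit: removing Holm leaves the tests insensitive to moderate rates. The size of the Holm family is open too. Local and systemic reactions are assessed separately, so it may be smaller than the full list of terms, which is why a range is shown.

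A reader might go further and fault the model itself, which is specified "with Treatment Group and Time as fixed effects, and subject and times within subject as random effects": no treatment-by-time term is listed, and the within-subject effect may overlap the residual. That is not a finding here. The section describes itself as brief, leaves the covariance structure to be chosen, defers detail to an analysis plan that is not shown, and repeats the analysis on change from baseline. Section 9.1.3.1 uses the same shorthand and still plans contrasts at each time point.

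None of this defends the two rules. Both are fixed in the text, and the protocol's own small-sample argument applies at least as strongly to safety.

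**Conclusion.** The point holds for two stated rules and no further. Holm's correction removes much of the limited power of the adverse-event comparisons: at 80% vs 10% it falls from 83% to between 53% and 17% over 5 to 50 terms, and at 50% vs 0% from 39% to 7% or less. It also contradicts the protocol's reasoning for immunogenicity. The sizes rest on an assumed two-sided 5% level, assumed numbers of terms and 6 controls; the direction does not depend on them. Separately, the laboratory and vital-sign model is selected on the outcome, and group shifts below an undefined threshold are never modelled. The change should be made, but the descriptive safety outputs and the trial's safety oversight do not depend on either rule.

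**What to change.** **Adverse events.** Remove Holm from Section 9.1.2, or keep it only as a secondary display. Report each incidence with an exact 95% interval, and the risk difference from pooled control with an exact 95% interval. Keep unadjusted Fisher p-values as flags only, and state that a non-significant result is not evidence of safety.

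**Laboratory and vital signs.** Delete the conditional opening. Summarise and analyse every scheduled parameter by group over time for all volunteers, including the worst post-dose grade.

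**Cost.** Wording and a few more tables; no extra volunteers, visits or blood. There will be more false flags, at most about 5% per term and dose comparison, to be reviewed clinically.
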